**Charlson Comorbidity Variables**			
Myocardial Infarction	410.*, 412.*	I21.*, I22.*, I25.2*	Quan, 2005 [20]
Congestive Heart Failure	398.91, 402.01, 402.11, 402.91, 404.01, 404.03, 404.11, 404.13, 404.91, 404.93, 425.4, 425.5, 425.7, 425.8, 425.9, 428*	I09.81, I11.0*, I13.0*, I13.2*, I42.0*, I42.5*-I42.9*, I43.*, I50.*	Quan, 2005 [20]
Peripheral Vascular Disease	093.0*, 437.3*, 440.*, 441.*, 443.1*, 443.2*, 443.8*, 443.9*, 447.1*, 557.1*, 557.9*, V43.4*	A52.01*, E08.51, E08.52, E09.51, E09.52, E10.51, E10.52, E11.51, E11.52, E13.51, E13.52, I67.0*, I67.1*, I70.*, I71.*, I73.1*, I73.8*, I73.9*, I77.7*, I79.*, K55.1*, K55.8*, K55.9*, Z958.2*	Quan, 2005 [20]
Cerebrovascular Disease†††	430*, 431*, 432.*, 433.*, 434.*, 435.*, 436*, 437.*, 438.*	G45.0, G45.1, G45.2, G45.4, G45.8, G45.9, G46.*, I60.*-I63.*, I65.*-I66.*, I67.1*, I67.2*, I67.4*, I67.5*, I67.6*-I67.7*, I67.81, I67.82, I67.84, I67.89, I67.9*, I68.*-I69.*	Quan, 2005[20]
Dementia	290.*, 294.1*, 331.2*	F01.*, F02.*, F03.9*, G31.1*	Quan, 2005 [20]
Chronic Pulmonary Disease	416.8*, 416.9*, 490*, 491.*, 492.*, 493.*, 494.*, 495.*, 496*, 500*, 501*, 502*, 503*, 504*, 505*, 506.4*, 508.1*, 508.8*	I27.2*, I27.81, I27.89, I27.9*, J40.*-J44.*, J45.2*-J45.5*, J45.90, J45.99, J47.*, J60.*, J61.*-J67, J68.4*, J70.1*, J70.2*, J70.3*, J70.4*, J70.8*	Quan, 2005 [20]
Connective Tissue Disease	446.5*, 710.0*, 710.1*, 710.2*, 710.3*, 710.4*, 714.0*, 714.1*, 714.2*, 714.8*, 725*	M05.*, M06.*, M31.5*, M31.6*, M32.*-M34.*, M35.0*, M35.3*, M36.0*	Quan, 2005 [20]
Peptic Ulcer Disease	531.*, 532.*, 533.*, 534.*	K25.*-K28.*	Quan, 2005 [20]
Mild Liver Disease	070.22, 070.23, 070.32, 070.33, 070.44, 070.54, 070.6*, 070.9*, 570*, 571.*, 573.3*, 573.4*, 573.8*, 573.9*, V42.7*	B17.9*, B18.0*-B18.2*, B19.0*, B19.9*, K70.0, K70.1*, K70.2, K70.3*, K70.40, K70.9, K71.*, K72.00, K73.*, K74.0*, K74.1*-K74.6*, K75.2*-K75.4*, K75.8*, K75.9*, K76.0*-K76.5*, K76.89, K76.9*, K77.*, Z48.23, Z94.4*	Quan, 2005 [20]
Diabetes without complications	250.0*, 250.1*, 250.2*, 250.3*, 250.8*, 250.9*	E10.1*, E10.618, E10.62*, E10.63, E10.64, E10.65, E10.69, E10.8*, E10.9*, E11.0*, E11.1*, E11.618, E11.62-E11.65, E11.69, E11.8*, E11.9*, E13.00, E13.01, E13.10, E13.11, E13.618, E13.62-E13.65, E13.69, E13.8*, E13.9*	Quan, 2005 [20]
Diabetes with complication	250.4*, 250.5*, 250.6*, 250.7*	E10.2*-E10.5*, E10.610, E11.2*-E11.5*, E11.610, E13.2*-E13.5*, E13.610	Quan, 2005 [20]
Paraplegia and Hemiplegia	334.1*, 342.*, 343.*, 344.0*, 344.1*, 344.2*, 344.3*, 344.4*, 344.5*, 344.6*, 344.9*	G04.1*, G11.4*, G80.*-G82.*, G83.0*-G83.4*, G83.9*	Quan, 2005 [20]
Renal Disease	403.01, 403.11, 403.91, 404.02, 404.03, 404.12, 404.13, 404.92, 404.93, 582.*, 583.0*, 583.1*, 583.2*, 583.4*, 583.6*, 583.7*, 585.*, 586*, 588.0*, V42.0*, V45.1*, V56.*	I12.0, I13.11, I13.2*, N03.*, N05.2*-N05.5*, N05.9*, N06.2*-N06.5*, N07.2*-N07.5*, N08.*, N17.1*, N17.2*, N18.*, N19.*, N25.0*, Z48.22, Z49.0*, Z49.3*, Z94.0*, Z99.2, Z91.15	Quan, 2005 [20]
Non-metastatic cancer	140.*, 141.*, 142.*, 143.*, 144.*, 145.*, 146.*, 147.*, 148.*, 149.*, 150.*, 151.*, 152.*, 153.*, 154.*, 155.*, 156.*, 157.*, 158.*, 159.*, 160.*, 161.*, 162.*, 163.*, 164.*, 165.*, 170.*, 171.*, 172.*, 174.*, 175.*, 176.*, 179*, 180.*, 181*, 182.*, 183.*, 184.*, 185*, 186.*, 187.*, 188.*, 189.*, 190.*, 191.*, 192.*, 193*, 194.*, 195.*, 200.*, 201.*, 202.*, 203.*, 204.*, 205.*, 206.*, 207.*, 208.*, 238.6*	C00.*-C26.*, C30.*-C34.*, C37.*-C41.*, C43.*, C45.0*-C45.2*, C45.7*, C45.9, C46.*-C58.*, C60.*, C61.*, C62.0*, C62.1*, C62.9*, C63.*-C76.*, C81.*-C86.*, C88.2*-C88.4*, C88.8*, C88.9*, C90.*-C93.*, C94.0*, C94.1*, C94.2*, C94.3*, C94.8*, C95.*, C96.0*, C96.2*, C96.4*, C96.9*, C96.A, C96.Z, D03.*, D45.*, D47.Z9	Quan, 2005 [20]
Moderate to severe liver disease	456.0*, 456.1*, 456.2*, 572.2*, 572.3*, 572.4*, 572.8*	I85.*, K70.41, K71.11, K72.01, K72.1*, K72.9*, K76.6*, K76.7*	Quan, 2005 [20]
Metastatic cancer	196.*, 197.*, 198.*, 199.*	C77.*-C80.*	Quan, 2005 [20]
HIV/AIDS	042*, 043*, 044*	B20.*	Quan, 2005 [20]
Depression	296.2*, 296.3*, 296.5*, 300.4*, 309.*, 311*	F31.3*-F31.5*, F31.75, F31.76, F32.*, F33.*, F34.1*, F43.10, F43.11, F43.12, F43.2*, F43.8*, F43.9*, F93.0*, F94.8*);	Quan, 2005 [20]
Drug abuse	292.*, 304.*, 305.2*, 305.3*, 305.4*, 305.5*, 305.6*, 305.7*, 305.8*, 305.9*, V65.42	F11.*-F16.*, F18.*, F19.*, Z71.41, Z71.6, Z71.51	Quan, 2005 [20]
Psychoses	293.8*, 295.*, 296.04, 296.14, 296.44, 296.54, 297.*, 298.*	F06.*, F20.*, F22.*-F25.*, F28.*, F29.*, F30.2*, F31.2*, F31.5*, F32.3*, F33.3*, F44.89, F53.*	Quan, 2005 [20]

^†^Claims data do not sensitively identify patients with hyperlipidemia. One prior validation study showed that this code was 32% sensitive/100% specific for hyperlipidemia [22].

^††^Claims data do not sensitively identify tobacco use, though are highly specific [23].

^†††^ The Quan, 2005 algorithm uses ICD-9-CM 362.34 (transient retinal artery occlusion) and ICD-10-CM H34.0 (transient retinal artery occlusion) as part of the algorithm for identifying cerebrovascular disease; we have removed these specific codes from our comorbidity list due to the possibility that CRAO may have been miscoded as 362.34 or H34.0 due to similar clinical presentation.

### Analytical cohort

An analytic cohort will be generated by applying the below inclusion and exclusion criteria as follows:

All patients meeting the criteria for AF in the study period and meeting other inclusion/exclusion criteria will be identified as cases, and the date of AF diagnosis will serve as case’s index date for calculation of covariates. All remaining beneficiaries will be considered potential controls; inclusion and exclusion criteria will be applied based on an index date of July 1 for each year in the study period; all beneficiaries meeting inclusion/exclusion criteria for each year will be included in the potential control pool. For all potential controls with multiple index dates/years of eligibility, the year they contribute will be selected randomly. A multivariable logistic regression analysis will be conducted using cases and potential controls to create propensity scores for AF status; the final control group will be selected using propensity score matching to the AF cases.

Survival time for patients will be defined as the number of months from the index date when criteria were met. Patients will be censored at death, at the end of fee-for-service enrollment, or at the end of data availability. When 85% of the cohort has died or been lost to follow-up, we will censor remaining patients at that point to avoid instability in estimates due to very small numbers of remaining participants.

Details of the cohort analysis will be reported using RECORD guidelines for analyses of routinely collected data, including use of a patient flow diagram [24].

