### Design and setting

Retrospective, observational, population-level cohort study of patients with atrial fibrillation and matched controls using administrative claims data among a 5% sample of fee-for-service Medicare beneficiaries in the United States from 2000–2020. This data source allows us to follow unique patients longitudinally for the duration of their fee-for-service enrollment, regardless of state of residence.

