### Inclusion and exclusion criteria (Aim 1)

The inclusion criterion is continuous fee-for-service Medicare enrollment for at least 12 months prior to AF diagnosis or matched index date (July 1 of inclusion year) for controls and continuous enrollment in fee-for-service (FFS) Medicare after AF diagnosis/index date for at least 12 months or until death if death occurred before 12 months of continuous enrollment.

Patients with prevalent AF will be identified as follows:ICD-9-CM code 427.31 or ICD-10-CM code I48 in 2 outpatient claims or 1 inpatient claim within 365 days, in any diagnosis position of the claim [16–18]. The index date will be the date of the first qualifying inpatient claim or second qualifying outpatient claim. Patients will be required to have 12 months of FFS claims without an AF diagnosis prior to the index AF claims based on inclusion criteria.

Exclusion criteria are:

patients with any claim for CRAO in the 12 months prior to AF diagnosis or index date for controls (July 1 of potential inclusion year).

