1) We will repeat the primary analysis, classifying CRAO based on the presence of the ICD codes in any diagnosis position rather than the primary diagnosis position.2) We will perform a sensitivity analysis for any retinal artery occlusion, using ICD-9-CM codes 362.3, 362.30, 362.31, 362.32, 362.33 and ICD-10-CM codes H34.9, H34.233, H34.1x, H34.0x, H34.12, H34.13, H34.23x, H34.21x) [31].i) We will perform a secondary analysis of patients with CRAO who later developed atrial fibrillation, to assess the hypothesis that clinically undetected paroxysmal AF may be associated with CRAO.j) Table shell for Aim 1 regression results are provided in Tables 6 and 7. The primary outcome is underlined.k) To address confounding resulting from patients potentially receiving a competing therapy (left atrial appendage occlusion, a procedural alternative to long-term oral anticoagulation), we will exclude patients with ICD-9-CM procedure code 37.90 or ICD-10-CM 02L73DK either in the follow-up period or in the ascertainment period.

**Table 6 pone.0296251.t006:** Crude and adjusted rates of CRAO in patients with and without atrial fibrillation.

	AF		No AF		AF	No AF	Rate Difference (95% CI)	aHR (95% CI)
	Patients with event	Rate per 1000 Or 100,000 Person-years	Patients with event	Rate per 1000 Or 100,000 Person-years	Adjusted rate per 1,000 person-years	Adjusted rate per 1,000 person-years		
CRAO (Overlap weighted)								
CRAO (primary Dx)								
Any RAO								
Ischemic stroke								
UTI								

**Table 7 pone.0296251.t007:** Hazard ratios for atrial fibrillation vs. no atrial fibrillation for Aim 1.

Outcome	Unadjusted Model	Adjusted Model†
CRAO (Overlap weighted)	HR (95% CI)	aHR (95% CI)
CRAO (primary dx)	HR (95% CI)	aHR (95% CI)
Any RAO	HR (95% CI)	aHR (95% CI)
CRAO (any dx position)	HR (95% CI)	aHR (95% CI)
Ischemic Stroke	HR (95% CI)	aHR (95% CI)
UTI	HR (95% CI)	aHR (95% CI)

^†^This column reflects the results of a model that incorporates overlap weighting using propensity scores re-estimated after our first stage matching procedure.

We will report a figure showing the adjusted cumulative incidence of CRAO according to AF vs. No AF groups using an overlap-weighted cumulative incidence function.

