#### Regression modeling (aim 2)

a) In keeping with target trial emulation methodology as described above, the index date for patients exposed to anticoagulation will be the date of the first anticoagulant prescription drug claim occurring after the diagnosis of AF. For potential controls, only patients with no exposure to anticoagulation throughout the study period would be eligible to avoid selecting controls who start an anticoagulant during the follow-up period. For controls, inclusion and exclusion criteria will be examined for each year after AF diagnosis, and the midpoint of one random year will be selected as the index date for each control patient.b) Similar to Aim 1, patients diagnosed with CRAO precedent to or concurrent to AF diagnosis will be excluded and these patients will be examined in an exploratory analysis.c) Our primary analysis will utilize propensity score overlap weighting methodology to approximate a randomized design where baseline hazard of CRAO of patients receiving anticoagulation vs. not receiving is comparable. We will incorporate the following variables to define the propensity score: age, time since first AF claim, sex, geography, race, Medicaid dual eligibility, vascular comorbidities and non-vascular comorbidities relevant to the likelihood that a patient will be treated with anticoagulation (to include all of the comorbidity variables included for Aim 1 propensity score, as well as history of gastrointestinal bleeding or peptic ulcer disease (using validated ICD-9-CM codes 531.x (gastric ulcer), 532.x (duodenal ulcer), and 578.x (gastrointestinal hemorrhage) and their ICD-10-CM counterparts K25.x, K26.x, and K92.2) and history of intracranial hemorrhage (any of ICD-10-CM I60, I61, S06.3, S06.4, S06.5, S06.6 and their ICD-9-CM counterparts 430.x, 431.x, 432.x)) [32–35].d) Our principal effect of interest is the hazard of CRAO among patients treated with any oral anticoagulant agent compared to those not treated. Given variable patient adherence to anticoagulation, we will take advantage of the strength of Part D data (which records pharmaceutical fills rather than prescriptions) and treat anticoagulation exposure as a time-varying covariate for patients exposed to anticoagulation.e) We will perform identical sensitivity analyses as described in Aim 1.f) Table shells for the results of Aim 2 are shown in Table 8.

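### Aim 1 controls are chosen on whether AF is diagnosed after their index date, so CRAO followed by AF drops out of the control rate; if CRAO prompts AF detection, the AF hazard ratio is biased upward

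*Protocol article*

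**What the plan says.** The Analytical cohort section builds the Aim 1 groups in order. First, "All patients meeting the criteria for AF in the study period and meeting other inclusion/exclusion criteria will be identified as cases". Then, "All remaining beneficiaries will be considered potential controls; inclusion and exclusion criteria will be applied based on an index date of July 1" of each study year, with one eligible year drawn at random per person. The study period is long: a "5% sample of fee-for-service Medicare beneficiaries in the United States from 2000–2020".

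Follow-up rules are the same for both groups: "Patients will be censored at death, at the end of fee-for-service enrollment, or at the end of data availability". AF onset in a control is not among the reasons for censoring, and no switch to exposed status is described.

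Two further rules govern CRAO that comes before AF. The Aim 1 exclusion criteria remove "patients with any claim for CRAO in the 12 months prior to AF diagnosis or index date for controls". In Regression modeling (aim 2), item b describes Aim 1 in the same spirit: "Similar to Aim 1, patients diagnosed with CRAO precedent to or concurrent to AF diagnosis will be excluded". In Regression modeling (aim 1), item i gives these patients a separate analysis: "We will perform a secondary analysis of patients with CRAO who later developed atrial fibrillation". Its stated purpose is to test whether undetected paroxysmal AF is linked to CRAO.

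**The concern.** A person who is AF-free in 2005 and first qualifies for AF in 2015 cannot serve as a 2005 control, because the AF group has already claimed that person. Membership of the comparison group is thus decided partly by what happens after time zero.

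This is harmless if later AF has nothing to do with CRAO. It is not harmless if a CRAO leads to a cardiac work-up and so to an AF diagnosis. In that case control events are removed selectively, the control rate is too low, and AF can look like a risk factor even if it is not. The error would favour the Aim 1 hypothesis. Matching and overlap weighting would not reveal it, since both act on baseline covariates and cannot undo selection on a post-index event.

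**Working it through.** **Where a CRAO followed by AF is counted.** Take a person AF-free on July 1 of some year, with CRAO later and an AF diagnosis after that.

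- Control arm: not eligible, because AF criteria are met within the study period.
- AF arm, CRAO within 12 months before AF: barred by the Aim 1 exclusion.
- AF arm, CRAO more than 12 months before AF: the person may enter under the Aim 1 criteria, but the CRAO lies before the index date and is not an outcome event. Under the wording in the Aim 2 section the person would be excluded.
- Item i: the person is studied separately, and the event does not go back into the control rate.

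In no branch is the event counted in the main comparison.

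**Plan's own figure.** The article gives no number for this mechanism. Its one Aim 1 calculation, 570,000 people for a hazard ratio of 2, is not disputed here and serves only for scale. Freedman's formula (two-sided 0.05, 90% power) needs 95 events. Divided by the mean yearly risk (22 + 11)/2 = 16.5 per 100,000, this is 575,758 people, within 1.0% of 570,000, on one year of follow-up without the stated 20% loss. Conversely, 570,000 × 0.000165 is about 94 events.

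**Size of the bias.** Let f1 be the share of control CRAO patients later diagnosed with AF before the data end, and f0 the same share in comparable people without CRAO. Selecting never-AF controls keeps a fraction 1−f1 of the events and about 1−f0 of the person-time. The control rate is multiplied by (1−f1)/(1−f0), and the hazard ratio by

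bias factor = (1−f0)/(1−f1).

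The document gives neither share, so both are assumptions. With f0 = 10%:

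- f1 = 10%: 0.90/0.90 = 1.00
- f1 = 20%: 0.90/0.80 = 1.125
- f1 = 30%: 0.90/0.70 = 1.29
- f1 = 40%: 0.90/0.60 = 1.50

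**Simulation check, true ratio 1.** Assumptions: 6,000,000 people, 8 years, 5% yearly mortality, AF incidence 1.5% or 3% per year. CRAO was set at 110 per 100,000 per year, ten times the plan's control rate, to reduce noise. The excess is the share of CRAO patients given an AF diagnosis soon afterwards because of the CRAO. Ranges cover the two AF incidences.

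| Assumed excess | Never-AF controls (as written) | AF-free at index, censored at AF |
|---|---|---|
| 0% | 0.99–1.01 | 0.99–1.01 |
| 5% | 1.03–1.05 | 0.99–1.00 |
| 10% | 1.07–1.12 | 0.97–1.01 |
| 20% | 1.20–1.24 | 0.97–1.00 |
| 30% | 1.35–1.41 | 0.96–1.00 |

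The formula agrees. At 1.5% AF incidence and 20% excess, the simulated shares were f0 = 5.6% and f1 = 23.9%, so 0.944/0.761 = 1.24. The true rate over the never-AF control rate was also 1.24. A second simulation (4,000,000 people, up to 20 years, AF 2% per year, AF-arm rate held at its true value) gave 1.04, 1.10, 1.21 and 1.37 for 5, 10, 20 and 30%.

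**Consequence for the test.** With a true ratio of 1 and a bias factor of 1.21, the chance of a significant ratio above 1 is Φ(½√D × ln 1.21 − 1.96) for D events in equal groups: 15% at D = 94, 57% at 500 and 85% at 1,000, against a nominal 2.5%. Larger D is plausible. The 818,940 AF patients found in the 2000–2015 query, at 11 per 100,000 per year, would give about 90 events per arm per year if all qualified.

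**The case against.** **The direction is conditional.** A reader might infer that the hazard ratio is certain to be inflated. The document does not support that. It plans to test a link between CRAO and later AF and reports no share of CRAO patients in whom AF is then found. With no excess detection the simulated ratio is about 1.0. This objection stands.

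**Item i cuts both ways.** If undetected AF caused the CRAO, the person was not truly AF-free at the event, and a simulation with a true ratio of 1 does not represent that case. This stands as a limit on the figures. If the target were true rather than diagnosed AF, undetected AF among controls would pull the ratio down, and the net error is not quantified here. But the plan defines exposure by claims and starts AF follow-up at the qualifying claim. On that definition a CRAO before that date is unexposed experience, and dropping it selectively lowers the control rate.

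**The word remaining could be read literally.** An AF patient who fails another case criterion would then fall back into the control pool, and a reader might infer that prevalent AF dilutes the effect. The same reading would return people with CRAO in the 12 months before AF to the pool, and bias from that group would run downward. The two claims cannot be held together. The Aim 2 remark on how Aim 1 treats CRAO before AF, and the Table 3 column for people without AF, both speak against the literal reading. The dilution claim is therefore not made here.

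**Perhaps people with future AF may be controls.** Then nothing censors or switches them at AF onset, and exposed time would count as unexposed. That reading needs a correction too.

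**Some safeguards exist.** The urinary tract infection endpoint could give a warning if hospital contact in general prompts AF detection. Neither it nor item i restores the lost events. The ischemic stroke positive control is open to the same mechanism, so reproducing a stroke association would not rule the bias out. No listed sensitivity analysis changes the control definition.

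**The size is modest against a design ratio of 2.** True at low detection shares. The calculations also leave out matching, weighting, the 12-month post-index enrollment rule and the 85% censoring rule.

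**Conclusion.** The point holds in conditional form. The Aim 1 control group is selected on AF diagnosed after the index date, and CRAO followed by AF is missing from the control rate. If CRAO raises the chance of a later AF diagnosis, the AF hazard ratio is biased upward by about (1−f0)/(1−f1). For assumed excess detection of 5, 10, 20 and 30% this is roughly 1.04, 1.1, 1.2 and 1.4 under a true ratio of 1; with no excess there is no material bias. These sizes rest on assumed detection shares and simplified simulations. They show that the choice can matter, not how much it will matter in these data. It affects the main Aim 1 contrast, and no planned analysis would correct it.

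**What to change.** Rewrite the control definition in the Analytical cohort section as follows:

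- Select controls on AF status at the index date alone: no AF in the look-back, whatever happens later.
- Censor controls at the date they meet the AF definition, or switch them to exposed with a new index date.
- Count CRAO before that date in the control arm.
- Use a person-level robust variance if people can contribute to both arms.
- Keep never-AF controls as a sensitivity analysis; the gap between the two results shows how much the choice matters.
- Add one sentence that anyone with AF at or before index cannot be a control.

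The cost is wording, additional coding and somewhat shorter control follow-up. No new data are needed.

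### Aim 1 controls are limited to people never diagnosed with AF in 2000–2020, so control eligibility depends on later events and the AF hazard ratio may be biased, probably upward

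*Protocol article*

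**What the plan says.** The Analytical cohort section builds the groups in order.

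- Cases come first: "All patients meeting the criteria for AF in the study period and meeting other inclusion/exclusion criteria will be identified as cases". Design and setting gives the period: "fee-for-service Medicare beneficiaries in the United States from 2000–2020".
- Controls come from what is left: "All remaining beneficiaries will be considered potential controls".
- A July 1 index date is then assigned: "For all potential controls with multiple index dates/years of eligibility, the year they contribute will be selected randomly".
- Follow-up ends as follows: "Patients will be censored at death, at the end of fee-for-service enrollment, or at the end of data availability". AF onset in a control is not listed, which fits a never-AF control group.

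Two places deal with CRAO that precedes AF. Item i of Regression modeling (aim 1) says: "We will perform a secondary analysis of patients with CRAO who later developed atrial fibrillation". Item b of Regression modeling (aim 2), described there as similar to Aim 1, says that "patients diagnosed with CRAO precedent to or concurrent to AF diagnosis will be excluded and these patients will be examined in an exploratory analysis". The Aim 1 exclusion itself reaches back only one year: "patients with any claim for CRAO in the 12 months prior to AF diagnosis or index date for controls".

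**The concern.** Whether someone may be a control on, say, July 1, 2005 should depend on what is known by that date. Under this plan it depends on whether AF is diagnosed at any point up to 2020. Baseline matching and overlap weighting cannot repair selection on an event after the index date.

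The removed person-time need not be neutral. Item i proposes that undetected paroxysmal AF may be associated with CRAO. If so, CRAOs are more frequent in the people removed, and the comparator rate is too low. This bears on the primary Aim 1 estimate. It matters the more because the team's earlier hospital-based study, described in the Introduction, found an inverse relationship, and the new study is meant to settle the question.

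**Working it through.** **1. One person traced through the rules.** AF-free on July 1, 2005; CRAO in 2007; AF diagnosed in 2012. The person is an AF case, because no CRAO falls in the 12 months before diagnosis. Follow-up starts in 2012, so the 2007 CRAO is not counted there. As a case, the person is not a remaining beneficiary and cannot be a control. The AF-free years and the CRAO enter neither arm of the primary comparison.

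Now let AF follow the CRAO within 12 months. The person fails the case criteria and, read literally, stays in the control pool, where the event can count. Item b of the Aim 2 modelling section points instead to exclusion. Both readings are calculated below.

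**2. When the rule is harmless.** Let λ be the CRAO rate in never-AF people, p the share of AF-free person-time that belongs to future AF cases, and r their pre-diagnosis CRAO rate relative to λ. The full AF-free rate is (1 − p)λ + prλ; the planned comparator has λ. Hence

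planned HR / HR with all AF-free time = 1 + p(r − 1).

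| p | r = 1 | r = 1.5 | r = 2 | r = 3 |
|---|---|---|---|---|
| 0.10 | 1.00 | 1.05 | 1.10 | 1.20 |
| 0.20 | 1.00 | 1.10 | 1.20 | 1.40 |
| 0.30 | 1.00 | 1.15 | 1.30 | 1.60 |

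The documents give neither p nor r.

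**3. A model with explicit rates.** All inputs are assumptions: true HR 1, death d = 0.05/year, AF diagnosis a = 0.015–0.035/year, horizon T = 8–12 years, CRAO rare, and AF diagnosis k times as frequent after a CRAO. The probability that AF is not diagnosed before death or within u years, at AF hazard h, is

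S(u, h) = d/(d + h) + [h/(d + h)]·exp(−(d + h)u).

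With all later-AF people removed and a lasting rise,

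factor = ∫₀ᵀ e^{−(a+d)t} S(T−t, a) dt ÷ ∫₀ᵀ e^{−(a+d)t} S(T−t, ka) dt.

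For example, with a = 0.035 and u = 12:

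- S(12, 0.035) = 0.588 + 0.412·e^{−1.02} = 0.737;
- with k = 3, S(12, 0.105) = 0.323 + 0.677·e^{−1.86} = 0.428.

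A person with an early CRAO is much less likely to remain never-AF, and so less likely to be kept as a control. For a one-year rise, the hazard is ka in the first year after CRAO and a afterwards. For the 12-month reading, AF in the first year after CRAO does not remove the person.

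| AF detection after CRAO | All later-AF people removed | AF within 12 months of CRAO stays in pool |
|---|---|---|
| No link (k = 1) | 1.00 | 0.96–0.99 |
| Doubled for one year | 1.01–1.03 | 0.96–0.99 |
| Tripled for one year | 1.03–1.07 | 0.95–0.98 |
| Doubled, lasting | 1.06–1.19 | 1.03–1.09 |
| Tripled, lasting | 1.12–1.41 | 1.06–1.21 |

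A simulation of 4 million people with true HR 1 (AF 2%/year, death 5%/year, CRAO rate raised 20-fold for precision) agrees. The planned HR was 1.00 with no link. It was 1.08 or 1.22 when AF was found within two years of 10% or 20% of CRAOs, and 1.00 or 1.07 if people with AF within 12 months stayed in the pool.

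**4. Effect on the test.** The plan states no figure for this bias. Its sample size section implies 285,000 × (22 + 11)/100,000 = 94 events per year of follow-up without loss. With true HR 1 and a factor of 1.2, the two-sided 5% test has z = (√94/2)·ln 1.2 = 0.884 and rejects with probability Φ(0.884 − 1.96) = 0.14. At an assumed 500 events this is 0.53.

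**5. The control endpoints.** Strokes before a later AF diagnosis leave the comparator in the same way, and the Aim 1 criteria do not exclude prior stroke. The positive control is thus pushed in its expected direction and would look reassuring. The urinary tract infection endpoint could flag general selection from removing future AF patients, but not a CRAO-specific link.

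**The case against.** A reader might infer that the hazard ratio is inflated as a matter of fact. The documents do not support that. With no link the factor is 1.00, and under the 12-month reading with no link or a one-year rise it falls slightly below 1. The larger figures need AF detection to stay raised for the whole of follow-up, whereas a diagnostic work-up after CRAO would concentrate it early. Shorter follow-up shrinks the bias too: with a lasting doubling, five years gives 1.04–1.09 with everyone removed and 1.01 under the 12-month reading. These objections stand.

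A reader might also infer that these events simply vanish. They do not: the plan assigns CRAO followed by AF to separate analyses. Those analyses, however, do not return the person-time or events to the primary comparator.

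The strongest counter-argument is occult AF. If item i is right, some of these people already had AF when the CRAO occurred, and counting them as unexposed pulls the hazard ratio toward the null. Excluding them keeps the comparator cleaner. This stands as a real cost of the fix and a reason to keep the never-AF group as a sensitivity analysis. It does not justify selecting primary controls on a later diagnosis, which also removes future AF cases whose AF had not begun.

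**Conclusion.** The selection fault is in the text: control eligibility at July 1 depends on AF diagnosed afterwards, and the AF-free experience of future AF cases is missing from the comparator. Upward bias is the expected direction under the plan's own hypothesis, but it is conditional on a higher pre-diagnosis CRAO rate after weighting. Neither sign nor size can be derived from the documents. Under the assumptions above the factor runs from 0.95 to 1.41, and most scenarios are modest against the hazard ratio of 2 used for power; in none of them does the bias alone produce a ratio of that size. This should be fixed before the primary analysis. It does not by itself invalidate the study.

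**What to change.** - Judge control eligibility only on information up to the July 1 index date: AF-free to date and meeting the other criteria, whether or not AF is diagnosed later.
- Censor such controls, or switch them to exposed, on the date they meet the Aim 1 case definition (first qualifying inpatient or second qualifying outpatient claim). Using the first AF claim would let an event fall between the arms. Eligibility and censoring must change together: admitting future cases without ending their control time at AF would bias toward the null.
- Revisit the random choice of one index year. Once AF onset cuts short the eligible years, drawing one year from them again depends on the future. With true HR 1, the simulation gave 0.92 and 0.89 in the 10% and 20% scenarios. Letting each person enter at every eligible July 1 avoids this.
- Cluster the variance by person.
- Keep the never-AF control group as a sensitivity analysis, for this outcome and for the control endpoints.
- Reconcile the Aim 1 exclusion criterion, the Analytical cohort section and item b of the Aim 2 modelling section on CRAO before AF.

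The cost is a change to cohort code and one censoring rule, with no new data. The downsides are that some people appear in both arms and that some re-admitted controls may have occult AF, which pulls toward the null.
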